**F. Secondary outcomes:**

Secondary outcomes of interest at the final follow-up will include number of quit attempts since enrollment, the number of smoked cigarettes/bidis per day (for those who were not able to quit), duration of use of intervention. The tobacco use outcomes will be smoking excess, smoking reduction, continued use and relapse from the baseline information. Interim smoking cessation outcomes at 3 and 6 months of intervention will be assessed.

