**G. Sample size:**

In a study conducted to find the efficacy of preloading combination NRT over standard combination NRT, 6-month sustained abstinence was 47.5% for the intervention group and 27.5% for the control group with a level of significance of 5%, power of 80% in the two-sided test [15.]. This proportion was considered to calculate the sample size for the current study. Eventually, the sample size was derived at 91 in each arm. By considering a loss to follow up of 10% in each arm, the sample size is 100.1 and hence rounded off conveniently to 100 per arm.

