| Health related quality of life                                           | 0-Day, 6 months, 12 months                                                                                                                                                                                                                                                                                                                   | 0-Day, 6 months, 12 months                                                                                                                                                                                                                                                                               |
| Saliva cotinine test                                                     | 0-day, Month- 3, 6, 12                                                                                                                                                                                                                                                                                                                       | 0-day, Month- 3, 6, 12                                                                                                                                                                                                                                                                                   |

**K.Statistical Analysis:** The collected information will be summarized by using frequency and percentage for qualitative data, mean and standard Deviation for quantitative data. To compare the outcome measures, quantitative before and after intervention, paired-t test will be used. If data is not following normal distribution, Wilcoxon Signed Rank test will be used. To compare qualitative outcomes, Chi-square test or Fischer exact test will be used. To compare the difference in outcome measures between two intervention groups, independent sample 't' test will be used. If data is not following normal distribution, Mann Whitney test will be used. The P value less than 0.05 will be considered as statistically significant.

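### Quantitative outcomes with a day-0 value are compared between arms without baseline adjustment, which costs precision, and cigarettes per day is defined only in non-quitters, so comparing it between arms is not a randomised comparison

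*Protocol*

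**What the plan says.** Section K (Statistical Analysis) gives two rules for quantitative outcomes. For change over time: "To compare the outcome measures, quantitative before and after intervention, paired-t test will be used", with the Wilcoxon signed-rank test if the data are not normal. For the arms: "To compare the difference in outcome measures between two intervention groups, independent sample 't' test will be used", with Mann-Whitney as fallback. Neither rule names a covariate.

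Day-0 values are scheduled. The table in section J lists CO, Fagerström score and smoking frequency at day 0 and months 1, 3, 6, 9 and 12, and quality of life at "0-Day, 6 months, 12 months". Section I adds body weight at each visit.

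Section F lists three quantitative secondary outcomes: quit attempts since enrolment, duration of use of the intervention, and "the number of smoked cigarettes/bidis per day (for those who were not able to quit").

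The Results paragraph after section K commits the trial to intention to treat. The one between-arm regression named there is a mixed-effects logistic model for the dichotomous outcome, used only if missing data exceed 10%. The survival analysis there concerns relapse. Neither touches the quantitative outcomes.

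**The concern.** There are two separate problems.

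**Precision.** When an outcome is also measured at day 0, part of its follow-up variance is predictable from that value. A two-sample t-test on final values leaves all of it in the error term, and a t-test on change scores removes it only imperfectly. The paired test does not fill the gap, because a before/after change mixes treatment with time, the counselling given to both arms, and regression to the mean.

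**Selection.** Not having quit is the complement of the primary outcome. If preloading works, the two groups of non-quitters are no longer exchangeable: the experimental arm has lost more of its participants to quitting. If lighter smokers quit more readily, those left in the experimental arm are heavier on average for reasons unrelated to any effect on their smoking. Testing that difference between arms does not fit the stated intention-to-treat principle, and a larger sample does not remove the bias.

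**Working it through.** **Inputs from the protocol.** Section G: "6-month sustained abstinence was 47.5% for the intervention group and 27.5% for the control group". The design there is two-sided at the 5% level with 80% power. Non-quitters are therefore 100 − 47.5 = 52.5% and 100 − 27.5 = 72.5%. Section G then states: "Eventually, the sample size was derived at 91 in each arm".

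**Reproducing the protocol's figure.** The two-proportion formula with pooled variance and no continuity correction, at 47.5% v 27.5%, two-sided 5% and 80% power, gives 91 per arm (power 80.1%). The figure reproduces. The protocol gives no sample-size figure for any quantitative outcome, so 91 serves below only as a reference size.

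**Step 1: precision.** Let r be the correlation between the day-0 and follow-up values. The protocol gives none, so a range is assumed. Take equal variances at the two times and set the variance of a t-test on final values to 1.
- t-test on change scores: 2(1 − r)
- ANCOVA: 1 − r²
- ANCOVA relative to change scores: (1 − r²) / [2(1 − r)] = (1 + r)/2

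| r (assumed) | ANCOVA / final value | Cut | ANCOVA / change score | Cut |
|---|---|---|---|---|
| 0.3 | 0.91 | 9% | 0.65 | 35% |
| 0.5 | 0.75 | 25% | 0.75 | 25% |
| 0.7 | 0.51 | 49% | 0.85 | 15% |

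In terms of power at 91 per arm, take an effect of 0.415 SD, for which the t-test on final values has 80%. ANCOVA has 83.6%, 89.9% and 97.5% at these correlations; the change-score t-test has 65.8%, 80.0% and 95.1%.

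This step does not apply to quit attempts since enrolment or duration of use, which have no day-0 value.

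**Step 2: who remains in the cigarettes-per-day comparison.** At the protocol's rates, 0.525 × 91 = 47.8 experimental and 0.725 × 91 = 66.0 control participants remain.

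**Step 3: size of the selection bias.** Assumptions, none of them from the protocol except the quit rates and the minimum of 10 cigarettes per day at entry:
- Baseline smoking is normal with mean 20 and SD 8, clipped to 10–60.
- The log-odds of quitting fall by 0.04, 0.08 or 0.12 per cigarette.
- Continuing control smokers smoke 0.7 × baseline, plus noise with SD 3. Continuing experimental smokers do the same, less any true reduction.

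Differences are experimental minus control, in cigarettes per day:

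| Slope | Non-quitters, no true reduction | Non-quitters, 5% true reduction | Non-quitters, 10% true reduction | All randomised, quitters = 0, no true reduction in continuing smokers |
|---|---|---|---|---|
| −0.04 | +0.3 | −0.5 | −1.2 | −2.8 |
| −0.08 | +0.6 | −0.2 | −1.0 | −2.7 |
| −0.12 | +0.8 | about 0 | −0.8 | −2.6 |

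If quitting is unrelated to baseline smoking, the non-quitter difference with no true reduction is 0. At 100 per arm the standard error of the non-quitter difference is about 1.08, so the shift is 0.3/1.08 to 0.8/1.08, roughly 0.3 to 0.75 standard errors. At 490 per arm the standard error would be 1.08 × √(100/490) = 0.49 and the shift roughly 0.6 to 1.6 standard errors.

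**Step 4: a second set of assumptions.** Baseline mean 20, SD 7, minimum 10; continuing smokers at 80% of baseline; odds of quitting lower by a factor of 1, 1.5, 2 or 3 per SD of baseline. With no effect in continuing smokers the non-quitter difference is 0.0, +0.47, +0.75 and +1.04. With a 5% true reduction it is −0.80, −0.38, −0.13 and +0.14. With 10% it is −1.60, −1.23, −1.01 and −0.77. The sign reverses only at the 5% reduction with the strongest gradient.

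**The case against.** **The unadjusted test is valid.** Correct. Under randomisation it is unbiased, and the loss is precision only. Its size depends on correlations the protocol does not give. Covariate adjustment is often settled in a SAP, which may exist here. But the protocol names the test, so a SAP that follows it inherits the choice.

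**Baseline may not be ignored.** The between-arm sentence follows the before/after sentence, so the difference in outcome measures may mean change scores. A reader might infer that baseline plays no part; the text does not settle that. Both readings are covered in step 1, and ANCOVA is more precise under each.

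**Few listed secondary outcomes have a baseline.** Also correct. Of the three quantitative outcomes in section F, only cigarettes per day has one. CO, Fagerström score and weight are scheduled measurements. Quality of life is an objective, worded as change due to cessation, for which a before/after analysis has its own purpose. The paired tests can stay for that, but they do not estimate the effect of preloading.

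**Section F and intention to treat may repair the restriction.** Section F also lists baseline-referenced categories such as smoking reduction and relapse, which are not restricted to non-quitters. Those are different outcomes, and the intention-to-treat statement conflicts with the cigarettes-per-day definition without changing it.

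**Sign reversal.** A reader might infer that an effective treatment will appear to increase smoking. The calculations do not support that. The positive differences assume no effect in continuing smokers and are under one standard error at 100 per arm. At a 5% true reduction they are negative or close to zero in nearly every scenario, and at 10% clearly negative in all. What stands is a bias in one direction, given that heavier smokers quit less often.

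**Trial size.** A reader might also argue from a small trial of 200. Section G gives 100 per arm, but section C gives 490 per arm and section H 245 blocks of four (980). The point does not depend on which is right.

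**Conclusion.** The point holds in two parts, both confined to secondary measures.

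1. For outcomes with a day-0 value, the named between-arm test is valid but inefficient. The variance that ANCOVA would save is 9% to 49% against final values, or 35% to 15% against change scores, for assumed correlations from 0.3 to 0.7. This is lost precision, not bias.

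2. Cigarettes per day is defined in a group selected after randomisation, so any between-arm test of it is not a randomised comparison and does not fit intention to treat. If heavier smokers quit less often, the comparison is biased against the arm with more quitters, by about +0.3 to +0.8 cigarettes per day under the step 3 assumptions (up to about +1.0 under step 4). If quitting is unrelated to baseline smoking there is no such shift. The usual consequence is attenuation of a real reduction; reversal of sign needs that reduction to be small.

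**What to change.** In section K, make the between-arm analysis of each quantitative outcome with a day-0 value an ANCOVA with that value as covariate. For quality of life at 6 and 12 months, use a repeated-measures model with baseline as covariate. State that the paired before/after tests are descriptive as regards treatment effect.

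In section F, define the between-arm comparison of cigarettes per day in all randomised participants, with abstainers counted as 0, adjusted for day-0 smoking frequency and with robust or bootstrap intervals. Report the non-quitter mean by arm descriptively. Baseline adjustment within non-quitters alone would not cure the selection. State how missing consumption values are handled, since section G allows for 10% loss to follow-up.

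Cost: wording only; the data are already scheduled. The downside is that the all-randomised result largely reflects the difference in quit rates, is skewed by the zeros, and does not say how much continuing smokers smoke. The descriptive non-quitter mean is kept for that.

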#### C. Recruitment of participants:

Patients and/or visitors of the hospital will be screened for tobacco use. Those who are known tobacco smokers will be advised to register for cessation services at the tobacco cessation center. The smoking cessation trial aims to recruit 490 participants in each arm. The participants will be enrolled based on the eligibility (all current smokers aged 18 years and above with a motivation to quit). Before randomization, smokeless tobacco users, smoking frequency of less than 10 cigarettes per day, pregnant women, lactating women, patients with recent history of myocardial infarction of less than 3 months, and electronic cigarette users will be excluded from the study. Further to this, randomization will be done to allocate participants to the appropriate study arms. The participant information sheet will be given and explained to the participants by the investigator about the risks and benefits of participating in the trial.

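### A normality check on the trial data chooses between a test of means and a rank test for each quantitative outcome, while the only stated summary is mean and SD, so the P value may not belong to the reported estimate

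*Protocol*

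**What the plan says.** Protocol section 3.K (Statistical Analysis) fixes three things for quantitative data.

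- **Summary:** "mean and standard Deviation for quantitative data". No median, quantile or rank-based estimate is named.
- **Before-after comparison:** paired t test, with the switch "If data is not following normal distribution, Wilcoxon Signed Rank test will be used".
- **Comparison between arms:** independent-samples t test, with the switch "If data is not following normal distribution, Mann Whitney test will be used".

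It does not say how normality is judged, at what level, or on what (raw values, differences, residuals, each arm separately).

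The outcomes exposed to the rule are secondary. Section 3.F lists the number of quit attempts, cigarettes per day among those who did not quit, and duration of use of the intervention. Sections 3.I and 3.J add Fagerström score, body weight and quality of life. Several are measured repeatedly: Fagerström score at day 0 and months 1, 3, 6, 9 and 12, and quality of life at day 0, month 6 and month 12. The primary outcome in section 3.E is binary and falls under the chi-square or Fisher test.

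**The concern.** The t test and the Mann-Whitney test address different quantities: the first a difference in means, the second whether values in one arm tend to rank above those in the other. When the arms differ only by a shift, the two usually agree. When they differ in shape, they need not.

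Under section 3.K the choice is made after the data are seen, outcome by outcome, and the descriptive statistic stays the mean in either case. Two consequences follow:

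- A reader may see a significant P value beside two nearly equal means, or the reverse, with no estimate on the page to which the P value belongs.
- The same outcome may be tested on means at one visit and on ranks at another, because the check can pass at one and fail at the other.

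Differences in shape are plausible here. A treatment that changes who quits, and how often people try, need not move every participant by the same amount.

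**Working it through.** **1. Sample size, to fix the n used below.** Section 3.G gives "6-month sustained abstinence was 47.5% for the intervention group and 27.5% for the control group", with "level of significance of 5%, power of 80% in the two-sided test". With the pooled-variance formula and p̄ = (0.475 + 0.275)/2 = 0.375:

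n = [1.960·√(2·0.375·0.625) + 0.842·√(0.475·0.525 + 0.275·0.725)]² / 0.20² = 90.8, rounded up to 91.

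This reproduces the plan: "Eventually, the sample size was derived at 91 in each arm". It rests on proportions and does not depend on the switch. Section 3.C instead "aims to recruit 490 participants in each arm", so 490 per arm is shown as well. Cigarettes per day is limited to non-quitters, about 91 × 0.525 = 48 and 91 × 0.725 = 66 per arm at the planning rates, so 50 per arm is also shown.

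**2. How often the t test survives a check.** Assumed rule: Shapiro-Wilk at 5% in each arm, with the t test kept only if both arms pass. All distributions are assumed.

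| Outcome type (assumed shape) | 50 per arm | 91 per arm | 490 per arm |
|---|---|---|---|
| Quit attempts (overdispersed count) | 0% | 0% | 0% |
| Cigarettes per day in non-quitters (negative binomial, mean 12) | 2% | 0% | 0% |
| Duration of use (capped) | 0% | 0% | 0% |
| Quality of life (left-skewed score) | 25% | 2% | 0% |
| Fagerström score | 55% | 3% | 0% |
| Change in Fagerström score | 52% | 14% | 0% |
| Body weight, mildly skewed | 57% | 31% | 0% |
| Exactly normal variable | 89% | 90% | 93% |

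**3. Is the switch needed to protect the error rate?** At 91 per arm, with identical skewed distributions in both arms, the simulated type I error of the t test was 4.7% to 5.2% over five assumed shapes. It is not needed for that purpose.

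**4. Mismatch between P value and means.** Take quit attempts as negative binomial with true mean m = 1.5 in both arms and dispersion (size) parameter k. Then the variance is m + m²/k, and the proportion with no attempt is (k/(k + m))^k:

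- k = 0.7: variance 1.5 + 2.25/0.7 = 4.71; proportion with none (0.7/2.2)^0.7 = 0.449
- k = 1.2: variance 1.5 + 2.25/1.2 = 3.38; proportion with none (1.2/2.7)^1.2 = 0.378
- k = 3: variance 1.5 + 2.25/3 = 2.25; proportion with none (3/4.5)^3 = 0.296

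Share of simulated trials with P<0.05 at 91 per arm:

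| k in the two arms | Mann-Whitney | t test |
|---|---|---|
| 0.7 v 0.7 (identical) | 5% | 5% |
| 0.7 v 1.2 | about 10% | 5% |
| 0.7 v 3 | about 28% | 5% |

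The normality check failed in every one of these data sets, so the Mann-Whitney column is also the result of the plan's rule. The means are equal throughout; the rank test responds to the difference in spread and in the proportion with no attempt.

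**The case against.** The case for leaving the text alone has real substance.

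- **The frequency rests on assumptions.** The protocol names no check and no distributions. A reader might infer that the t test will almost never be used for any quantitative outcome. The documents do not support that: body weight and change scores can keep it at about 91 per arm, and a near-normal variable keeps it in about 90% of data sets. This stands, and the point is limited to counts, duration and bounded scores.
- **The rank test is valid for its own question.** A reader might infer inflated false positives. With identical distributions there is no inflation. In the equal-mean cases the arms really do differ, and they were constructed with equal means. The cost is a P value without a matching estimate, not a false finding.
- **Exhaled CO is a weak example.** Section 3.F does not list it as an outcome, and section 3.D treats it as complementary, with a cutoff. Nor does an example that scores quitters as zero cigarettes fit, because section 3.F restricts that count to people who did not quit. Neither is relied on here.
- **Quality of life.** A reader might infer that the third objective, change in quality of life, is compromised. No mismatch has been calculated for it. The signed-rank test works on within-person differences, and where these are roughly symmetric it targets the same centre as the mean.
- **The statistical analysis plan is not shown.** It may name the check and an estimate to go with the rank test. That would ease the problem, but the protocol itself adopts the data-driven rule, so this is not merely a detail left for later.

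Mean and SD is also a general descriptive sentence; it does not bar a rank-based estimate. That is why the conclusion says the P value may not belong to the reported means, not that it cannot.

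**Conclusion.** The point holds in a limited form and is minor. Section 3.K lets the trial data choose between a test of means and a rank test for each quantitative secondary outcome, while the only stated summary fits one of the two. With a formal check at about 91 per arm, counts, duration and bounded scores would usually go to the rank test; measures closer to normal may not. The switch buys no protection, since the t test holds about 5% at this size.

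Where the arms differ in shape at equal means, the rank P value departs from the means: about 10% to 28% of trials significant in the quit-attempts example, against about 5% for the t test. These figures depend on Shapiro-Wilk at 5% per arm, negative binomial counts with mean 1.5, and the assumed dispersion gap; a smaller gap gives a smaller mismatch, and no gap gives none. The binary primary outcome and the sample size are untouched.

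**What to change.** In section 3.K, delete both sentences that switch the test on non-normality. Name one analysis for each quantitative outcome before data are seen, use it at every visit, and report an estimate with 95% CI that matches the test. One reasonable set:

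- quality of life, Fagerström score and body weight: mean difference (or mean change) from regression with robust standard errors;
- number of quit attempts: rate ratio from negative binomial regression;
- Mann-Whitney and Wilcoxon signed-rank: kept as named sensitivity analyses.

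Other choices would serve equally well, including prespecifying the rank test for an outcome together with a rank-based estimate and interval. What matters is that the choice is fixed and the estimate fits it.

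The cost is wording in the protocol, repeated in the analysis plan. No change to the sample size or data collection is needed. The small downside is some loss of power for some skewed outcomes, where a rank test can be more efficient.

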#### Methodology:

**A. Trial Design:** This randomized, controlled, two-armed, single-blinded, superiority trial with 1:1 allocation ratio is designed based on CONSORT 2010 Guidelines. This superiority trial intends to gather further evidence that combination nicotine replacement therapy is more efficient than a fast-acting NRT alone.

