**Results:** The study shall adopt the "Intention to Treat Analysis" mechanism. If the study has missing data more than 10% of the total sample size as expected during sample size calculation, Pattern-Mixture Model within a mixed-effects logistic regression model for longitudinal dichotomous data will be used. Because of the dichotomous outcome, logistic regression version of the mixed-effects model is applicable. The pattern-mixture effects for drug, time, data pattern and their interactions will be interpreted. Pattern mixture sensitivity analysis using SAS/STAT, missing data analysis will be done using R software, and survival analysis will be used to analyze the variation in smoking relapse over time related to the socio-demographics, smoking history, and treatment-related variables.

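### The pattern-mixture model is used only if missing data exceed 10%, the same figure as the planned loss, and its role beside the chi-square test is not settled

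*Protocol*

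**What the plan says.** Section E of the protocol sets a binary primary outcome, abstinence or not at 12 months. Section K gives the tests. For categorical outcomes: "To compare qualitative outcomes, Chi-square test or Fischer exact test will be used". The Results paragraph that follows adopts intention to treat without any condition. It then makes a pattern-mixture model, fitted within a mixed-effects logistic regression for repeated binary data, depend on what is observed: "If the study has missing data more than 10% of the total sample size as expected during sample size calculation". Effects of drug, time, data pattern and their interactions are to be interpreted. A later sentence in the same paragraph calls the pattern-mixture work a sensitivity analysis.

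The 10% comes from section G: "By considering a loss to follow up of 10% in each arm". No test is labelled primary, and nothing is triggered at or below 10%.

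**The concern.** The protocol states a rule here; this is not a detail left open. Whether the missing-data model is used at all depends on an observed count, and the cut-off sits at the value the design itself expects. With 200 randomised, moving from 20 to 21 missing participants changes what is done. The two methods also answer different questions. One compares proportions at 12 months. The other gives longitudinal model effects with pattern interactions, with no single 12-month contrast named.

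The threshold is also taken over the total sample. In a cessation trial loss may well be related to relapse, and what matters then is who is lost and from which arm. A pooled count carries neither piece of information. It can stay below the threshold while unequal loss changes the conclusion.

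**Working it through.** **Inputs.** Section G: "6-month sustained abstinence was 47.5% for the intervention group and 27.5% for the control group", with "level of significance of 5%, power of 80% in the two-sided test", and 10% loss per arm. Allocation is 1:1 (section A). Section G arrives at 100 per arm, 200 in total. Section C aims for 490 per arm, and section H has 245 blocks of four, so 980 in total. Both totals are carried below because the protocol does not reconcile them.

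**Step 1: reproduce the plan's figure.** Two proportions, pooled variance under the null:

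n = [1.96·√(2·0.375·0.625) + 0.842·√(0.475·0.525 + 0.275·0.725)]² / 0.20² = 90.8, so 91 per arm. This agrees with "the sample size was derived at 91 in each arm". Then 91 × 1.10 = 100.1, the plan's figure, rounded to 100.

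**Step 2: chance of crossing the trigger.** More than 10% means at least 21 of 200, or at least 99 of 980. Counting participants with a missing outcome and assuming independent dropout at true rate d, the chance is P(X > 0.10·N) with X ~ Binomial(N, d).

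| True loss d | N = 200 | N = 980 |
|---|---|---|
| 5% | 0.1% | 0.0% |
| 8% | 12% | 1.1% |
| 9% | 26% | 12.6% |
| 10% (planned) | 44.1% | 47.3% |
| 11% | 62% | 83% |
| 12% | 77% | 97% |
| 15% | 97% | 100% |

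**Step 3: unequal loss under a pooled threshold.** Assumed counts, 100 per arm, 20 missing in total. That is exactly 10%, so the trigger stays off. The counts come from completer quit rates of about 43% and 29%. All tests are chi-square without continuity correction.

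| Missing (exp. v control) | Completers | p | Missing = smoking | p |
|---|---|---|---|---|
| 10 v 10 | 39/90 v 26/90 | 0.044 | 39/100 v 26/100 | 0.0497 |
| 15 v 5 | 37/85 v 28/95 | 0.050 | 37/100 v 28/100 | 0.17 |
| 18 v 2 | 35/82 v 28/98 | 0.048 | 35/100 v 28/100 | 0.29 |

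For the 15 v 5 row:
- Completers: 0.4353 − 0.2947 = 0.1406. Pooled proportion 65/180 = 0.3611. SE = √[0.3611·0.6389·(1/85 + 1/95)] = 0.0717. z = 1.96 (unrounded p = 0.049996).
- Missing as smoking: 0.09 / √(0.325·0.675·0.02) = 0.09/0.0662. z = 1.36.

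The trigger treats the three rows alike.

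**Step 4: power if missing counts as non-abstinent.** With 10% missing in each arm the rates become 0.9 × 47.5% = 42.75% and 0.9 × 27.5% = 24.75%. At 100 per arm:

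power = Φ{[0.18 − 1.96·√(2·0.3375·0.6625/100)] / √[(0.4275·0.5725 + 0.2475·0.7525)/100]} = Φ(0.745) = 77.2%.

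Completers only, 90 per arm at the planned rates, give 79.7%. At 490 per arm, power exceeds 99.9% either way.

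**The case against.** The strongest reply is that nothing necessarily switches. No test is called primary, the text does not say the model displaces the chi-square test, and the same paragraph calls the pattern-mixture work a sensitivity analysis. A conditional supplement is an available reading. This stands, and it is why the point is put as an unsettled role plus a data-dependent trigger. It does not rescue the trigger: a sensitivity analysis run only above a chosen missing rate still depends on the data.

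The near-chance description also needs its condition. With 980 randomised, the question is nearly settled at 8% or 12% loss. It applies near 10%, which is the rate section G plans for.

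A statistical analysis plan, not shown, may hold a rule for missing outcomes. The absence of one here is therefore not held against the protocol. Such a plan would, however, have to override the stated trigger, not merely add detail to it.

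A reader might infer three stronger things that the documents do not support:
- **That intention to treat is abandoned at or below 10%.** It is declared without condition, and no completer analysis is stated. The completer figures above are only an illustration.
- **That the repeated outcome can only move one way, so that the mixed model cannot suit it.** Section E joins self-reported smoking and a positive cotinine test with an *and*. On the literal text, early smoking followed by a negative test is not non-abstinence. The protocol also does not say which binary series is modelled.
- **That there would be about two dropouts per arm in each pattern.** This needs 100 per arm, five visits and even dropout, at a loss of exactly 10%, which does not trigger the model. Cotinine after baseline is scheduled only at months 3, 6 and 12, and patterns are not defined and could be grouped.

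**Conclusion.** The point holds in this limited form. The protocol ties use of the pattern-mixture model to an observed missing rate above 10%, the loss it plans for. At that rate the chance of using it is 44% (N = 200) or 47% (N = 980), assuming independent dropout. Its standing relative to the chi-square or Fisher test is ambiguous. A threshold on the pooled rate gives no protection against unequal loss. The p-values of 0.050 and 0.17 show what can happen under assumed counts. They are not a forecast, and the first lies almost exactly on the significance boundary. The matter should be corrected before analysis, but it does not by itself undermine the design.

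**What to change.** Remove the 10% trigger. Name one primary analysis that applies whatever the missing rate: all randomised participants in their assigned arm, 12-month abstinence, missing status counted as non-abstinent, risk difference with 95% confidence interval, and chi-square test. Always run the pattern-mixture analysis, as a sensitivity analysis, varying the assumed abstinence among the missing separately in each arm. Separate variation is needed because counting the missing as smoking lowers both quit rates but need not be conservative for the difference when loss is unequal. If more controls are lost, it can favour the experimental arm.

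The cost is wording and modest analysis time. Reported quit rates will be slightly lower. At 100 per arm with 10% missing in each arm, power is about 77% against the planned 80%, and the protocol should say so.
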